## Abstract

**Background:**

Surgical conditions in laparoscopic surgery are largely determined by the depth of neuromuscular relaxation. Especially in procedures that are confined to a narrow working field, such as retroperitoneal laparoscopic surgery, deep neuromuscular relaxation may be beneficial. Until recently, though, deep neuromuscular block (NMB) came at the expense of a variety of issues that conflicted with its use. However, with the introduction of sugammadex, rapid reversal of a deep NMB is feasible. In the current protocol, the association between the depth of NMB and rating of surgical conditions by the surgeon and anesthesiologist is studied.

**Methods/design:**

This is a single-center, prospective, randomized, blinded, parallel group and controlled trial. Eligible patients are randomly assigned to one of two groups: (1) deep NMB (post-tetanic count, one or two twitches; *n* = 12) and (2) moderate NMB (train-of-four, 1 to 2 twitches, *n* = 12) by administration of high-dose rocuronium in Group 1 and a combination of atracurium and mivacurium in Group 2. The NMB in Group 1 is reversed by 4 mg/kg sugammadex; the NMB in Group 2 by 1 mg neostigmine and 0.5 mg atropine. Patients are eligible if they are over 18 years, willing to sign the informed consent form, and are scheduled to undergo an elective laparoscopic renal procedure or laparoscopic prostatectomy. A single surgeon performs the surgeries and rates the surgical conditions on a five-point surgical rating scale (SRS) ranging from 1 (poor surgical conditions) to 5 (excellent surgical conditions). The intra-abdominal part of the surgeries is captured on video and a group of five anesthesiologists and ten surgical experts will rate the videos using the same SRS. The primary analysis will be an intention-to-treat analysis. Evaluation will include the association between the level of NMB and SRS, as obtained by the surgeon performing the procedure and the agreement between the scoring of the images by anesthesiologists and surgeons.

**Discussion:**

We aim to show that under the right conditions the perceived opposing goals of surgeons and anesthesiologists (optimal surgical conditions vs. optimal postoperative conditions) may be met without compromise to either.

**Trial registration:**

ClinicalTrials.gov identifier NCT01631149.

## Background

Surgical conditions in laparoscopic surgery are largely determined by the depth of neuromuscular relaxation during surgery. Especially in procedures that are confined to a narrow working field, such as retroperitoneal laparoscopic surgery (for example*,* renal and prostatic laparoscopic surgery), deep neuromuscular relaxation may be beneficial. Until recently, however, deep neuromuscular block (DNB, one or two twitches post-tetanic count (PTC)) came at the expense of a variety of issues that conflicted with its use. For example, occurrence of residual postoperative neuromuscular blockade after deep neuromuscular block (DNB) is a common adverse event (AE). Residual NMB is a risk factor for developing airway obstruction, hypoxia, and pulmonary complications, such pneumonia and atelectasis [1]. The use of acetycholinesterase inhibitors, such as neostigmine, to reverse NMB, while beneficial, is relatively slow in onset of reversal. Furthermore, side effects due to acetylcholine-induced muscarine receptor stimulation are bradycardia, hypersalivation, nausea, and vomiting [2]. Coadministration of a muscarine agonist, such as atropine or glycopyrrolate, is often necessary to counteract some of these side effects. These agents, however, in themselves may induce other side effects. Moreover, recent studies indicate that high-dose neostigmine (>5 mg) is associated with postoperative complications, including the need for reintubation and muscle weakness [3,4].

Rapid, complete reversal of neuromuscular blockade was not possible until the discovery of sugammadex. Sugammadex is a modified γ-cyclodextrin. It was developed to selectively bind free plasma rocuronium, a nondepolarizing steroidal neuromuscular blocking agent [5]. By binding free rocuronium, less rocuronium becomes available at the neuromuscular junction to bind to the muscarinic receptor [6]. Nondepolarizing neuromuscular blocking agents (NMBAs), such as rocuronium, block the muscarine receptors at the neuromuscular junction, making them unavailable to acetylcholine-based signal transmission. Sugammadex has proven to reverse rocuronium-induced NMB rapidly [7-10]. Even high-dose rocuronium (1.2 mg/kg) and continuous rocuronium infusion used to achieve deep neuromuscular blockade can be reversed by sugammadex [11,12].

Additional secondary endpoints of the study include the effect of depth of NMB on economic parameters (time to optimal extubation conditions (TOF 4 with T1/T4 ratio >90%), time to extubation, duration of surgery, and time in the post-anesthesia care unit), perioperative hemodynamics, and postoperative conditions (respiratory rate, arterial oxygen saturation, pain, sedation).

We hypothesize that:

1. There is a positive association between the depth of NMB and the surgical condition as rated by the attending surgeon.

2. There is a disconnect between the perception of the surgeon and the anesthesiologist in the rating of the surgical conditions.

3. Reversal of a deep NMB with sugammadex leads to postoperative conditions similar or superior to the conditions obtained from reversal of a moderate NMB with neostigmine.

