### Sample size calculation

The sample size calculation is based on the expectations of the surgical rating score during surgery, as provided by an interview with the surgical expert (see Table 3).

**Table 3 T3:** Approximate expectations of SRS for the two treatment arms

**Score**	**Interpretation**	**Treatment group**	
		**Moderate block**	**Deep block**
5	Optimal conditions	10%	70%
4	Good conditions	20%	20%
3	Acceptable conditions	55%	10%
2	Poor conditions	10%	0%
1	Extremely poor conditions	5%	0%

These anticipated frequencies lead to an odds ratio of 21 for obtaining optimal conditions versus suboptimal conditions for deep block as compared with the moderate block condition. To obtain the power for a given sample size, ten thousand simulations were performed with moderate block as a fixed distribution and a simulated distribution of the deep block condition, assuming proportionality of the odds ratio with an odds ratio of 21 and analyzing the results with a proportional odds model using the score test. Results of the simulations are given in Table 4.

**Table 4 T4:** Approximate expectations for the two treatment arms

**Sample size per group (total)**	**Power***
7 (14)	82%
8 (16)	87%
9 (18)	90%
10 (20)	93%
11 (22)	95%
12 (24)	97%

Given uncertainty of the anticipated effect size, a sample size of 12 per group or 24 in total was considered prudent, in order to provide a sufficient margin.

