### Statistical analysis

The data analysis will be based on an intention-to-treat approach. For the SRS and other ordinal outcomes, the proportional odds model will be used, using the score test. If the proportionality of odds assumption is systematically violated, the data will be dichotomized for optimal conditions versus nonoptimal conditions. For continuous variables a general linear model will be used. Covariates can be included in these analyses when they provide an improvement of the model (when statistically significant at the 0.05 significance level, two-sided). Covariates to be considered are anesthesia or surgery related (for example, drug dosages, duration of surgery, BIS) and patient related (for example, age, weight, body mass index). Additional analyses will be performed on the secondary outcome parameters. To assess the agreement on the SRS across the various groups of raters the weighted kappa coefficient will be presented.

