## Discussion

This is the first trial to assess the relationship between the level of neuromuscular blockade and the rating of surgical conditions in laparoscopic retroperitoneal surgery. To reduce between-subject variability in the scoring system, a single surgeon was selected to perform the procedure and score the surgical conditions. The surgeon in our study has ample experience with the procedure. We argue that this allows for sufficient confidence in the reliability of the SRS. The scoring scale was constructed in close cooperation between researchers and surgeon and based on a series of study try-outs. A five-point scale allows sufficient discrimination between surgical conditions varying from poor (SRS = 1) to excellent (SRS = 5). While it is expected that a DNB provides improved surgical conditions in laparoscopic retroperitoneal surgery, its use has been limited, owing to anticipated negative consequences, including the need for high-dose neostigmine for reversal, longer reversal times with consequently longer turn-over times, a high probability of poor postoperative conditions with the possibility of residual neuromuscular blockade and all of its consequences (reduced ability to fend hypoxia, aspiration, pneumonia, and so on) and prolonged stay in the post-anesthesia care unit [1,14]. Rapid reversal of a DNB is made possible with the introduction of sugammadex. However, rapid reversal is only acceptable when postoperative conditions are not different from those observed after moderate NMB and reversal with neostigmine and recurarization does not occur. Our protocol will shed light on this issue, as additional (secondary) aims include the assessment of respiration and pulse oximetry, as well as other patient conditions, in the recovery period.

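### Secondary hypothesis 3 claims similar or superior postoperative conditions, but the named models look for differences in 12 versus 12 patients, so a non-significant result could be read as similarity

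*Protocol article*

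**What the plan says.** The Background of the protocol article lists three hypotheses. The third reads "Reversal of a deep NMB with sugammadex leads to postoperative conditions similar or superior to the conditions obtained from reversal of a moderate NMB"; the comparator agent is neostigmine. The same section places the outcomes concerned (respiratory rate, oxygen saturation, pain, sedation) among the additional secondary endpoints.

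Under Statistical analysis, ordinal outcomes go to a proportional odds model with the score test. For the rest, "For continuous variables a general linear model will be used". Secondary outcomes are also promised further analyses, which are not described. No margin and no equivalence or non-inferiority comparison is named.

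The Discussion says what result would make the strategy acceptable: "rapid reversal is only acceptable when postoperative conditions are not different from those observed after moderate NMB and reversal with neostigmine", and recurarization must not occur. The abstract gives the overall aim, that the goals of surgeon and anesthesiologist "may be met without compromise to either"; the end of the Discussion repeats it.

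On size, "The sample size calculation is based on the expectations of the surgical rating score during surgery", and "a sample size of 12 per group or 24 in total was considered prudent".

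**The concern.** To support a claim of similar or better, the data must rule out a relevant worsening. A test of no difference does not do that. It controls the risk of declaring a difference that is absent, and failing to reject says little when the sample is small. If the acceptability condition is that conditions are not different, and the tool at hand is a difference test in 24 patients, then the less precise the data, the easier the first half of that condition is to meet.

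What is at stake is the postoperative half of the without-compromise message. The Background and Discussion name residual block and its respiratory consequences as the reasons deep block has been used sparingly. Reassurance on these points that rests on wide intervals would be unsupported.

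**Working it through.** **The plan's own figure.** Table 3 gives optimal conditions in 70% (deep) and 10% (moderate): (0.70/0.30)/(0.10/0.90) = 21, as stated. The check applied a proportional odds ratio of 21 to the moderate-block distribution, with 10,000 simulated trials per sample size and the proportional odds score test. Two-sided 0.05 was assumed; the article states that level only for covariate selection.

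| n per group | 7 | 8 | 9 | 10 | 11 | 12 |
|---|---|---|---|---|---|---|
| Table 4 | 82% | 87% | 90% | 93% | 95% | 97% |
| Re-simulated | 81% | 86% | 90% | 93% | 95% | 97% |

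The stated power is sound, but it belongs to the surgical rating score at an odds ratio of 21. It does not carry over to any postoperative outcome.

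**Precision for a continuous postoperative outcome.** Inputs: 12 per arm (Sample size calculation), one summary value per patient, equal SDs, 22 degrees of freedom. The article gives no SDs, so results are in SD units.

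- Standard error of the difference: √(2/12) = 0.408 SD.
- 95% half-width: t(22; 0.975) × 0.408 = 2.074 × 0.408 = 0.85 SD.

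**Chance of a non-significant result when a true difference exists** (noncentral t, noncentrality = difference/0.408, two-sided 0.05):

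| True difference (assumed) | Power | Non-significant |
|---|---|---|
| 0.5 SD | 22% | 78% |
| 0.8 SD | 47% | 53% |
| 1.0 SD | 65% | 35% |

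Power of 80% needs a true difference of about 1.2 SD.

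**What a margin-based reading could deliver.** Margins are assumed in SD units, with true difference zero and one-sided 0.025 (normal approximation).

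| Margin (assumed) | Chance of success at 12 per arm | n per arm for 80% |
|---|---|---|
| 0.25 SD | 9% | 252 |
| 0.3 SD | 11% | 175 |
| 0.5 SD | 23% | 63 |
| 0.75 SD | 45% | 28 |
| 1.0 SD | 69% | 16 |

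The t-based chance of success is slightly lower: 22% at 0.5 SD and 65% at 1.0 SD.

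**Recurarization in the deep-block arm.** If 0 of 12 is observed, the exact upper limit for the true rate is:

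- one-sided 95%: 1 − 0.05^(1/12) = 22%
- two-sided 95%: 1 − 0.025^(1/12) = 26%

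At a true rate of 10%, 0.9^12 = 28% of trials show no event, so 72% show at least one.

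**Where this does not apply.** Sedation is scored on an ordinal 0 to 6 scale and falls under the proportional odds model, so the SD-based figures do not describe it. Recovery-room values are taken every 15 minutes, so the figures assume that these are first reduced to one number per patient.

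**The case against.** The strongest reply is that this is a secondary question in a small trial sized for something else, and that the article claims no postoperative power. A margin may stand in the full protocol or analysis plan. A general linear model yields estimates with confidence intervals, so interval reporting is already compatible with the text, and the unspecified further analyses leave room for more. All of this is fair, and for that reason the missing margin is not the point. What remains is what the article itself states: a similarity hypothesis, difference-type models, and an acceptability condition worded as not different.

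A reader might infer four stronger things that the document does not support:

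- **That non-significance will be taken as proof of similarity or safety.** No sentence says so. The phrase stands in the Discussion, not in a decision rule, and safety is not part of hypothesis 3. The most one can say is that the result could be read that way.
- **That the Discussion's condition is met automatically by a null result.** It also requires that recurarization does not occur, and a single event would breach it.
- **That harm would very likely be missed.** At a true recurarization rate of 10%, most trials (72%) would show at least one case, and a 1.0 SD difference would be detected 65% of the time. The risk of a miss is substantial for moderate effects, not near-certain for all.
- **That 0.5 SD is a clinically relevant worsening.** The document gives no basis for calling it so.

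**Conclusion.** The point holds as a weakness in how a secondary hypothesis is framed and judged. Read as written, the not-different wording lets low precision work in favour of the without-compromise aim. The interval for a continuous patient-level summary spans about ±0.85 SD, and twelve event-free patients leave a recurarization rate of up to 22% to 26% open. These figures rest on 12 analysed patients per arm, equal SDs, approximate normality and two-sided 0.05 (the one-sided limit excepted). The difference sizes and margins are illustrations only. The primary comparison of the surgical rating score and its stated 97% power are not affected. The change is worth making because it alters what may be concluded.

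**What to change.** 1. Recast hypothesis 3 as exploratory estimation.
2. Report each postoperative difference with its 95% confidence interval. For ordinal sedation, report the odds ratio with its interval.
3. Report recurarization as x/12 with its exact upper limit.
4. Replace the not-different wording in the Discussion with a statement that a non-significant result is not evidence of similarity.
5. Use similar or without compromise only for outcomes whose interval excludes a margin that the investigators set before seeing the data. Otherwise report the outcome as inconclusive.

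No extra patients or measurements are needed. The cost is a more modest postoperative claim: even if the arms are truly equal, results will most likely be inconclusive for margins clearly below 1 SD (45% chance of success at 0.75 SD), and a margin of 1 SD would still fail about one time in three.

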## Methods and design

The protocol (P12.101) of the study was approved by the local ethics committee (Commissie Medische Ethiek, Leids Universitair Medisch Centrum) and registered at clinicaltrials.gov under number NCT01631149. The study is performed in one center, Leiden University Medical Center. All procedures will be executed in compliance with the current revision of the Declaration of Helsinki and Good Clinical Practice/Good Research Practice (GCP/GRP) guidelines. The study is randomized (deep versus moderate block) and blinded (the surgeon and the team that scores the videos are blinded; the attending anesthesiologist is not blinded).

### Inclusion and exclusion criteria

Patients diagnosed with renal or prostatic disease who will undergo elective laparoscopic renal surgery or a prostatectomy are eligible for inclusion in the study. Exclusion criteria are: American Society of Anesthesiologist class IV; age <18 years; inability to give informed oral or written consent; known or suspected neuromuscular disorders impairing neuromuscular function; allergies to muscle relaxants, anesthetics or narcotics; a (family) history of malignant hyperthermia; a contraindication for neostigmine administration; pregnancy or breastfeeding; renal insufficiency, as defined by serum creatinine levels at twice the normal level, or urine output <0.5 ml/(kg h) for at least 6 h (when available, other indices will also be taken into account, such as glomerular filtration rate <60 ml/h and proteinuria (a ratio of 30 mg albumin to 1 g of creatinine)), previous retroperitoneal surgery at the site of the current surgery, or body mass index >35 kg/m [2].

### Investigational plan and treatments

Eligible patients will be randomly assigned to one of two study groups. Group 1 will receive DNB (PTC of one or two twitches) obtained with a loading dose of rocuronium of 1.0 mg/kg followed by a continuous infusion. The pump rate will vary and depends on the PTC value. The initial pump rate will be set at 0.6 mg/kg per h. In case of a deviation from the required PTC value the pump rate can be increased or decreased. Group 2 will receive moderate NMB (TOF of one or two twitches) obtained with a loading dose of atracurium of 0.5 mg/kg followed by a continuous infusion of mivacurium. The pump rate will vary and depends on the TOF value. The initial pump rate will be set at 0.5 mg/kg per h. In case of a deviation from the required TOF value, the pump rate can be increased or decreased. In case of extreme poor conditions (SRS = 1 or 2), both rocuronium and mivacurium infusion rates will be increased by 20% after a bolus administration of 15 mg.

Since the research team is blinded to the muscle relaxant used and the level of NMB, the attending anesthesiologist is responsible for both the administration of the muscle relaxant and the degree of NMB. He or she will not discuss the NMB with the surgeon or the research team.

After the surgery has finished, subjects who receive rocuronium will be reversed with sugammadex (4 mg/kg). Again, this will be known by the attending anesthesiologist only and will be blinded to surgeon and the research team. Subjects who receive atracurium and mivacurium will be reversed with neostigmine (1 to 2 mg) and atropine (0.5 to 1 mg). Patients will be extubated when the TOF ratio becomes 0.9 or larger.

See Figure 1 for a flow diagram of the study.

**Figure 1 F1:**
[figure not shown]
Study flow chart.

### Anesthesia

Induction and maintenance of anesthesia is by propofol combined with bolus doses of an opioid (sufentanil). Propofol will be given as bolus of 2 to 2.5 mg/kg, followed by a continuous infusion of 8 to 12 mg/kg per h. The propofol dose will be adjusted such that the bispectral index (BIS, Covidien, Mansfield, MA) is between 45 and 55. The opioid use will be at the discretion of the attending anesthesiologist and is administered in single bolus infusions of 0.25 to 0.6 μg/kg. For NMB, see above.

#### Video images

The video images will be collected from the camera connected to the endoscopic probe placed in the retroperitoneal field of surgery. The images collected are the images used by the surgeon to observe the surgical field throughout the procedure (these are his working images). Thus, the collected video images are identical to the image of the surgeon during the procedure. The video images will be edited into short 30-s snippets at 15-min intervals (corresponding with the moment of surgical scoring) plus additional frames from episodes in which sudden changes in surgical conditions occurred. The videos will be rated by surgical experts (five urological surgeons with expertise in laparoscopic surgery, five non-urological surgeons with expertise in laparoscopic surgery) and five anesthesiologists (with expertise in giving anesthesia for laparoscopic procedures). These experts are blinded to the level of NMB and have no knowledge of the study endpoints. The rating score will be identical to the surgical rating score (Table 1).

#### Neuromuscular monitoring

For neuromuscular function monitoring, the TOF-watch SX acceleromyograph (MSD BV, Haarlem, The Netherlands) at the adductor pollicis muscle will be used. The thumb is attached to a flexible adaptor that applies a constant preload to the thumb. Neuromuscular stimulation will be applied to the ulnar nerve via two pediatric electrodes applied on the skin left and right of the ulnar nerve at the distal underarm. Before administration of any neuromuscular blocking agent, but after induction of general anesthesia, the following procedures are conducted to standardize the neuromuscular monitoring: (1) application of a tetanic ulnar nerve stimulation (50 Hz for 5 seconds); (2) calibration of the TOF-watch (CAL 2); (3) performance of a series of TOF measurements, to ensure that the TOF ratio differs by less than 5% between measurements (if the TOF ratio differs by more than 5%, the TOF-watch will be recalibrated). After these steps, the neuromuscular blocking agent according to protocol is administered. When, during the study, the number of measured twitches is zero, the PTC will be measured. A 50 Hz tetanic stimulation for 5 s is followed (after a 3 s rest) by 15 single stimulations at 1 Hz. The number of twitches generated (that is, the PTC) corresponds with the degree of NMB, with a PTC of 1 to 2 reflecting a deep level of NMB.

